## Abstract

**Background:**

Approximately 180 million people worldwide, (3 % of the world’s population) are infected with hepatitis C (HCV). Insulin resistance (IR) and type 2 diabetes (T2DM) are common extrahepatic manifestations of chronic HCV infection and associated with poor treatment and liver-related outcomes. The presence of these metabolic complications have been associated with poor response to interferon-based HCV antiviral therapy and increased risk of liver-related outcomes. Metformin, an insulin sensitizer is known to improve HCV treatment response and has been associated with a reduced risk of developing hepatocellular carcinoma (HCC). This study will evaluate the effect of metformin on preventing progression or promoting regression of liver fibrosis, rate of virologic cure (SVR) and other metabolic measures in HCV-HIV co-infected and HCV mono-infected study participants who have IR and are planning on initiating HCV treatment.

**Methods:**

This study is a prospective 48-week single-centre, randomized, open-label, controlled trial of HIV-HCV co-infected and HCV mono-infected patients with IR (HOMA-IR ≥ 2.0) who are planning to initiate HCV antiviral therapy. Sixty participants will be recruited from The Ottawa Hospital Viral Hepatitis Clinic. Participants will be randomized in a 1:1 ratio to either arm 1, metformin 2 g (1 g twice daily) plus lifestyle, or to arm 2, lifestyle alone. The primary outcome will be the change in FibroScan® score (kPa) from baseline to week 12 (start of HCV treatment), the end of HCV treatment (week 24) and 24 weeks post HCV treatment (week 48). Secondary outcomes include changes in liver fibrosis using AST to platelet ratio index, changes in glucose and lipid levels, anthropometric measures, changes in alpha-fetoprotein levels, patient acceptability, and changes in dietary and physical activity parameters.

**Discussion:**

This pilot study will be the first to evaluate the role of metformin on liver fibrosis in HCV-HIV co-infected and HCV mono-infected patients with IR receiving DAA HCV treatment. If metformin is effective in reducing liver fibrosis in this patient population, this will represent a well-tolerated, easy-to-administer, inexpensive therapy that will protect against negative HCV outcomes. This study will also be an opportunity to evaluate the impact of insulin resistance and hyperglycemia on viral clearance in HCV-infected patients treated with interferon-free regimens.

**Trial registration:**

ClinicalTrials.gov NCT02306070 version 4.0 (June 29, 2015)

**Electronic supplementary material:**

The online version of this article (doi:10.1186/s13063-016-1454-6) contains supplementary material, which is available to authorized users.

## Background

Approximately 180 million people worldwide (3 % of the world’s population) are infected with hepatitis C (HCV) [1]. Although HCV mainly affects the liver, the virus is also associated with several extrahepatic manifestations including hematologic, autoimmune, dermatologic, and endocrine disorders [2]. Insulin resistance (IR) and type 2 diabetes (T2DM) are the most common endocrine disorders in HCV-infected individuals. This association was first demonstrated in HCV-infected individuals with cirrhosis compared with individuals with cirrhosis from other causes (prevalence of T2DM 50 % versus 9 %, respectively) [3]. HCV is believed to directly impact insulin signaling by interacting with specific proteins such as serine/threonine kinases that subsequently inhibit insulin signaling molecules [4]. HCV is also believed to indirectly cause insulin resistance by inducing the production of pro-inflammatory cytokines that impair insulin signaling pathways in uninfected tissues [5].

The presence of IR and T2DM in HCV has been associated with poor HCV antiviral treatment response [6–8], acceleration of liver fibrosis [9, 10], increased risk for hepatocellular carcinoma (HCC) [11], higher transplant complication rates [12], and possibly increased morbidity from cardiovascular and metabolic complications [13]. At least one observational study identified improved IR in genotype 1 HCV-infected patients achieving viral clearance with HCV antiviral therapy [14].

Hepatic fibrosis is a response to liver injury that arises from the activation of hepatic stellate cells (HSCs) by inflammatory cytokines. Once HSCs are activated, they further release cytokines that promote inflammation, fibrosis, contraction and mitosis [15]. Insulin resistance is a major determinant of liver fibrosis, however, the mechanism by which IR promotes liver fibrosis is not well established.

In recent years, the treatment of HCV has evolved with the development of direct-acting antiviral (DAA) therapies (protease inhibitors, NS5a inhibitors, and nucleotide and non-nucleotide polymerase inhibitors). Compared to interferon and ribavarin therapies alone, these new treatments are associated with significantly improved sustained virological response (SVR) rates, shorter treatment duration and more favourable side effect profile.

The effect of DAA HCV treatments on insulin resistance and long-term risk of type 2 diabetes has yet to be clearly established. A randomized controlled trial of HCV mono-infected study participants receiving 14 days of monotherapy with the protease inhibitor danoprevir, found that serum HCV RNA and homeostatic model assessment of insulin resistance (HOMA-IR) correlated significantly (Spearman rho = 0.379, *p* < 0.0001) [16]. At the end of 14 days of danoprevir monotherapy the mean decrease in HCV RNA was 2.2 ± 1.3 log10 IU/ml (*p* < 0.0001) in patients who received the active drug (*n* = 40), which correlated with a decrease in mean HOMA-IR score by 1.6 ± 1.1 (*p* < 0.0001). In contrast, HCV-RNA and HOMA-IR remained unchanged in placebo recipients. The role of insulin resistance and hyperglycemia as predictors of SVR with DAA HCV treatment has not been clearly established. There are also no studies to date that have examined the role insulin resistance or hyperglycemia play in promoting progression or preventing regression of liver fibrosis in patients that have achieved SVR with HCV antiviral therapy.

In high-risk populations, metformin, an insulin sensitizer, has been shown to delay or prevent the onset of T2DM [17]. While it is unknown whether this specific benefit extends to those infected with HCV, metformin does improve HCV treatment and liver-related outcomes. At least one study showed treatment with metformin resulted in higher SVR rates when compared with the control group (59.2 % vs. 38.8 %, chi-square 4.083, *p* = 0.043) [18]. HCV-infected patients with cirrhosis and T2DM who were taking metformin had a decreased risk of developing HCC [19, 20].

At the cellular level, metformin is highly concentrated in the liver and improves IR through the activation of AMP-activated protein kinase (AMPK) which decreases gluconeogenesis in the liver and increases glucose uptake in the skeletal muscle [21]. In vitro studies have demonstrated that pharmacologic activation of AMPK with metformin may have antifibrotic effects by inhibiting the transforming growth factor beta (TGF-β1)-induced fibrogenic property of HSCs via transcriptional coactivator p300 [22]. TGF-β1 is the most characterized of the fibrotic cytokines and has been found to be increased in HCV-HIV co-infected patients [23]. It has also been proposed that the anticancer effects of metformin in HCV-infected patients may also be via AMPK and the inhibition of mammalian target of rapamycin (mTOR), which in turn regulates cell cycle progression and cell growth [24]. There are no studies to date that have looked at the effect of metformin in preventing progression of liver fibrosis or accelerating regression fibrosis in patients treated with HCV antiviral therapy.

Alpha-fetoprotein (AFP) is an oncofetal protein associated with hepatic malignancies and liver regeneration [25, 26]. HCV core protein, inflammation, necrosis and hepatocellular injury have all been suggested as causes for elevated AFP levels in chronic HCV infection [25–28]. Although type 2 diabetes and insulin resistance have been identified as risk factors for the progression of liver fibrosis and development of hepatocellular carcinoma the mechanism by which this occurs is not clear [9, 11, 29, 30]. The relationship between AFP and insulin resistance was recently examined in a retrospective analysis of 300 HCV-infected patients [31]. This study demonstrated that whole-body insulin resistance and hepatic fibrosis correlated directly with elevated levels of AFP lifestyle modification over a 3-month period correlated with improved insulin resistance and a reduction in AFP levels. This study draws attention to the need for further prospective studies to understand the relationship between insulin resistance, AFP, hepatic fibrosis and hepatocarcinogenesis. No studies have examined the effect of metformin, an insulin sensitizer, on AFP levels.

While SVR is associated with improved liver outcomes, the rate of liver fibrosis regression with SVR is variable and predictors of regression are not well established [32]. In addition, achieving SVR in patients with cirrhosis does not necessarily prevent decompensation or eliminate the risk of HCC. A better understanding of the role insulin resistance and impaired glucose metabolism have on these outcomes in HCV patients who achieve SVR are needed.

Identifying and targeting potentially modifiable risk factors such as IR may be of significant importance in preventing progression of and promoting regression of liver fibrosis, reducing mortality and improving outcomes for HCV-HIV co-infected and HCV mono-infected patients.

Given the above body of evidence and the established safety of metformin in HCV and HIV, we developed a protocol to evaluate the effect of metformin on preventing progression or promoting regression of liver fibrosis, rate of virologic cure (SVR) and other metabolic measures in HCV-HIV co-infected and HCV mono-infected study participants who have IR and are planning on initiating HCV treatment.

## Methods

### Hypothesis

The use of metformin will slow the progression and promote regression of liver fibrosis in HCV-HIV co-infected and HCV mono-infected patients with impaired insulin sensitivity (defined as HOMA-insulin resistance > 2.0).

### Objectives

The primary objective of this study will be to evaluate the role of metformin in preventing progression and promoting regression of liver fibrosis in HCV-HIV co-infected and HCV mono-infected participants with IR receiving antiviral HCV treatment as assessed by transient elastography (FibroScan®, Echosens, Paris, France).

As secondary objectives we will evaluate the effect metformin has on virologic response rates based on SVR (i.e. 12 weeks post HCV antiviral treatment and its effect on the progression and regression of liver fibrosis using aspartate aminotransferase (AST)-to-platelet ratio index (APRI). We will additionally consider the effect of metformin and lifestyle modification have on metabolic parameters (fasting insulin, fasting glucose and fasting lipid levels), inflammatory markers [interleukin 6 (IL-6), interleukin 8 (IL-8), tumor necrosis factor alpha (TNF-α), TGF-β, C-reactive protein (CRP], anthropometric measurements [weight, body mass index (BMI), waist circumference], AFP levels, HCV viral status, human immunodeficiency virus (HIV) viral status and liver enzymes. Patient acceptability of metformin will be evaluated in arm 1 using a patient acceptability questionnaire. All participants will receive lifestyle and dietary counselling at baseline and at 24-week intervals. The effects of lifestyle modification will be evaluated using dietary and physical activity questionnaires.

### Study design and setting

This study is a prospective 48-week single-centre, randomized, open-label, controlled trial of HIV-HCV co-infected and HCV mono-infected patients with IR (HOMA-IR ≥ 2.0) who are planning to initiate HCV antiviral therapy.

Sixty (60) participants meeting eligibility criteria will be randomized in a 1:1 ratio using variable block sizes to either arm 1, metformin 2 g [1 g twice a day (BID)] plus lifestyle, or to arm 2, lifestyle alone (the control arm). Randomization will be stratified according to HIV status and according to stage of liver fibrosis (F0–2 vs. F3–4) and will be conducted utilizing a web-based randomization system. The allocations will be generated by a statistician unassociated with the study using the SAS statistical program (SAS Institute, Inc., Cary, NC, USA) and uploaded into the randomization system. A log of all transactions including date and time of randomization, stratum and treatment allocation will be recorded. The randomization system will be accessed by the study coordinator at the study site when they have identified consenting eligible participants ready to be randomized.

Arm 1 (Metformin group) will receive metformin and lifestyle treatment during a 12-week period prior to starting HCV therapy (week 0–12), during the 12-week treatment phase (week 12–24) and 24 weeks post HCV treatment (week 24–48). Participants who require > 12 weeks of HCV treatment will be excluded. If initiation of HCV treatment is delayed beyond 12 weeks, participants will continue on metformin during this time period and will receive less metformin post HCV treatment. Arm 2 (Control group) will receive lifestyle treatment alone during a 12-week period prior to starting HCV therapy (week 0–12), during the 12-week treatment phase (week 12–24) and 24 weeks post HCV treatment (week 24–48). A detailed study flow chart is depicted in Fig. 1.

**Fig. 1 Fig1:**
[figure not shown]
Flow diagram of study processes. Sixty participants meeting eligibility criteria will be randomized in a 1:1 ratio using variable block sizes to either arm 1, metformin 2 g (1 g BID) plus lifestyle (Metformin group), or to arm 2, lifestyle alone (Control group). *Abbreviations: HCV* hepatitis, *HIV* human immunodeficiency virus, *IR* insulin resistance*, BID* twice daily, *DAA* direct-acting antiviral therapy*, kPa* kilopascals

### Selection of participants

Participants will be recruited from The Ottawa Hospital Viral Hepatitis Clinic. Study recruitment will begin in July 2016. All adult patients between the ages of 18 and 79 years of age, who have provided informed consent, have documented history of chronic HCV RNA infection with evidence of fibrosis on FibroScan® > 8.0 kilopascals (kPa) or liver biopsy score > 2 (Batts-Ludwig System [33] within 2 years, insulin resistance as determined by a HOMA-IR of > 2.0 at screening and intend to start an 8–12 week interferon (IFN)-free HCV antiviral therapy. If participants are HIV-infected and not on HIV antiviral therapy, they will require a CD4 count of at least 200 to be included in the study.

Individuals will be excluded from the study if they are: pregnant, suspected to be pregnant, planning to become pregnant or breastfeeding, have a chronic HBV infection, an HbA1c > 8.0 %, are using immune-suppressing medications, have an active malignancy, are currently or previously treated with metformin or other oral diabetes medications or insulin, have a history of pre-existing diabetes (type 1, type 2 or gestational diabetes), clinical evidence of decompensated cirrhosis (ascites, esophageal varices, hepatic encephalopathy, hepatocellular carcinoma), renal impairment [serum creatinine levels > = 136 umol/L (males), > = 124 umol/L (females)], history of congestive heart failure requiring pharmacologic therapy, Wilson’s disease, alpha-1 antitrypsin, hemochromatosis, biliary cirrhosis, alcohol consumption > 50 g/day on average, participation in other clinical investigations during the study, or a history of lactic acidosis irrespective of precipitating factors.

Active illicit drug use (IDU) and stable health illness will not be exclusionary assuming it is unlikely to compromise study adherence to protocol and study drug. In HIV-infected participants, HIV antiretroviral use and suppressed HIV viral load will not be required for participation.

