### Metformin dosing

Arm 1 participants will be provided with the following recommended dose adjustments and advised to increase the dose accordingly: week 1: 500 mg once daily (QD); week 2: 500 mg BID; week 3: 500 mg three times daily (TID); week 4: 1 g BID or 500 mg QD. Participants will also be encouraged to administer their study treatment with food whenever possible to minimize the gastric intolerances. If participants are unable to tolerate an increase in dose, they will continue on the last dose tolerated.

Metformin dosing will additionally be based on renal function and dosed as follows:if creatinine clearance (CrCl) 30–60 mL/min, metformin will be reduced to 50 % of the dose or 500 mg BIDif CrCl < 30 mL/min, metformin will be stopped.

The potential side effects associated with metformin will be reviewed with each participant.

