^d^Tests to be done if not already in participant medical records [hepatitis B (HBV) needs to be within 6 months of screening visit; HIV needs to be within 1 month of screening]

^e^If results available within 1 month of screening visit, no need to retest

^f^Hematology: complete blood count (CBC) with differential, platelets, international normalized ratio (INR)

^g^Chemistry: electrolytes, aspartate aminotransferase (AST), alanine aminotransferase (ALT), gamma-glutamyl transferase (GGT), lipase, albumin, direct bilirubin, lactate, creatinine, estimated glomerular filtration rate (eGFR)

^h^Lipids: total cholesterol, high-density lipoprotein (HDL), low-density lipoprotein (LDL), triglycerides

^i^Anthropometric measures: height, weight, body mass index (BMI), waist circumference, hip circumference, waist-to-hip ratio. At screening, only height and weight documented

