### Safety assessments

Metformin has been studied in both HCV and HIV mono-infected patients with no increase in adverse events (AE) [18, 34]. Metformin does have the potential risk of lactic acidosis. A reduced dose (50 % of maximal dose) is used for patients with a CrCl < 60 mL/min. It is not recommended for use in patients with a creatinine clearance of < 30 mL/min. Patients will be cautioned against excessive alcohol intake, either acute or chronic when taking metformin, since alcohol intake potentiates the effect of metformin on lactate metabolism [35, 36].

A Data and Safety Monitoring Committee (DSMC) will be implemented to safeguard participant safety. All members will be independent from the study investigators. This committee will conduct regularly scheduled meetings to review the study progress including recruitment and conduct, and will identify any potential safety signals in the study population.

At each contact with the participant, information regarding adverse events (AEs) will be elicited by appropriate questioning and examinations. Any AE that occurs between the time that the participant is randomized and the time that s/he departs the study at the end of the final follow-up visit (or at the time of early withdrawal of the participant from the study for any reason) is to be recorded. Participants will also be monitored during the 48-week study period for serious adverse events (SAEs). If an SAE is ongoing at the time a participant discontinues/completes the trial, the SAE will be followed until the investigator agrees that the event is satisfactorily resolved, becomes chronic, or that no further follow-up is required (Table 1). 

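### Renal eligibility is set on serum creatinine but metformin is reduced or stopped on creatinine clearance, and nothing makes the two rules agree

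*Protocol article*

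**What the plan says.** Three parts of the protocol article deal with renal function, on three different measures.

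- **Entry (Selection of participants).** The only renal exclusion is "renal impairment [serum creatinine levels > = 136 umol/L (males), > = 124 umol/L (females". It takes no account of age or weight, and the age range is wide: "All adult patients between the ages of 18 and 79 years of age".
- **Dosing (Metformin dosing).** The first rule is "if creatinine clearance (CrCl) 30–60 mL/min, metformin will be reduced to 50 % of the dose", with 500 mg twice daily as the stated alternative. The second is "CrCl < 30 mL/min, metformin will be stopped".
- **Safety (Safety assessments).** Both limits are restated on the clearance scale: "A reduced dose (50 % of maximal dose) is used for patients with a CrCl < 60 mL/min" and "It is not recommended for use in patients with a creatinine clearance of < 30 mL/min". Lactic acidosis is named as the risk.
- **Laboratory panel (Table 1, footnote g).** The chemistry panel, scheduled at screening, baseline and every later visit, includes "creatinine, estimated glomerular filtration rate (eGFR". No rule uses the eGFR.

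Study design and setting defines arm 1 as metformin 2 g/day plus lifestyle. The article gives no formula for CrCl and does not relate the creatinine cut-offs to the clearance limits.

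**The concern.** A fixed creatinine value corresponds to very different clearances depending on age, sex and weight. When entry is judged on one scale and treatment on the other, a person can pass screening and be randomised while already meeting the protocol's own rule for reducing, or even stopping, the drug.

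The effect on the analysis is limited but real. The intention-to-treat set is everyone randomised, so such an arm 1 participant stays in the primary comparison untreated or on a reduced dose and dilutes the contrast. Adherence is judged against the maximum tolerated dose, so someone on a renally reduced dose may still count as adherent, and the per-protocol analysis would not necessarily remove the dilution. The planned subgroup comparing full with less than full dose is meant to show whether lower doses do as well. Its lower-dose group would include people placed there by baseline renal function, and so also by age, sex and weight.

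**Working it through.** The plan states no clearance figure or formula, so there is none to reproduce. The check asks which clearances are compatible with the stated entry rule.

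**Inputs from the article.** Exclusion starts at 136 umol/L (men) and 124 umol/L (women), so the highest eligible whole values are 135 and 123. Ages run from 18 to 79. The reduced-dose band is CrCl 30–60 mL/min and the stop limit is below 30.

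**Assumptions.** The formula and the body weights are not in the article. Cockcroft-Gault is taken first, then CKD-EPI (2009) and MDRD as sensitivity checks.

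**Cockcroft-Gault:** CrCl = (140 − age) × weight × k / creatinine, with k = 1.23 for men and 1.04 for women. At the highest eligible creatinine:

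| Person | Calculation | CrCl (mL/min) | Protocol's own rule |
|---|---|---|---|
| Woman, 79 y, 50 kg | 61 × 50 × 1.04 / 123 | 25.8 | stop |
| Woman, 70 y, 50 kg | 70 × 50 × 1.04 / 123 | 29.6 | stop |
| Man, 79 y, 50 kg | 61 × 50 × 1.23 / 135 | 27.8 | stop |
| Woman, 50 y, 70 kg | 90 × 70 × 1.04 / 123 | 53.3 | reduce |
| Man, 60 y, 70 kg | 80 × 70 × 1.23 / 135 | 51.0 | reduce |
| Man, 70 y, 80 kg | 70 × 80 × 1.23 / 135 | 51.0 | reduce |

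*Width of the stop overlap.* Solving for the weight at which CrCl = 30 gives weight = 30 × creatinine / ((140 − age) × k).

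- Women at 123: 58.2 kg at age 79, 54.6 kg at 75, 50.7 kg at 70.
- Men at 135: 54.0 kg at age 79, 50.7 kg at 75, 47.0 kg at 70.

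Only people lighter than this, with creatinine close to the cut-off, fall below 30.

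*Width of the reduced-dose overlap.* With 60 in place of 30, at age 60, men up to 82.3 kg and women up to 88.7 kg at the highest eligible creatinine are in the band. The overlap also reaches well below the cut-off. A 70-year-old of 70 kg has CrCl 60 at creatinine 70 × 70 × 1.23 / 60 ≈ 100 (man) or 70 × 70 × 1.04 / 60 ≈ 85 (woman).

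**eGFR instead of CrCl.** With s = creatinine / 88.4:

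- CKD-EPI above its creatinine knot: 141 × (s/κ)^−1.209 × 0.993^age (× 1.018 for women), κ = 0.9 for men and 0.7 for women. At age 79 and the highest eligible creatinine it gives 42.7 (man) and 35.9 (woman).
- MDRD: 175 × s^−1.154 × age^−0.203 (× 0.742 for women). It gives 44.2 (man) and 36.5 (woman).

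Neither formula uses weight, and both fall with age and creatinine, so these are the lowest values an eligible person can have. Neither reaches 30. Both lie inside the reduced-dose band.

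**Number affected.** The article gives no distribution of age, weight or creatinine, so no count or effect on power can be computed. With 60 randomised 1:1, one such participant is 1/30, about 3 %, of arm 1.

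**The case against.** The strongest reply is that the protocol already handles this. It enrols people with moderately reduced clearance and gives them a prespecified reduced dose. The regimen is titrated, lower tolerated doses are allowed, and a dose subgroup is planned. That reply stands: the reduced-dose overlap is not a contradiction. It leaves open whether the sponsor meant to randomise people who cannot reach the arm's defining dose.

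The second reply is that the stop overlap depends on a formula the article does not name. That also stands. Under Cockcroft-Gault it needs greater age, low weight and creatinine near the limit all at once. Under eGFR, the only renal estimate the article lists, it disappears.

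The third is that a journal article may leave the formula and the pre-dose check to the full protocol. The missing formula alone would indeed be no finding. But the article states both the entry rule and the dosing rule, and they are not aligned as written.

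A reader might go further and infer that patients below the clearance limit would be given metformin without protection. The documents do not support this. Creatinine and eGFR are measured at screening, baseline and each later visit, and the dosing rule stops the drug below 30 whoever was enrolled. Nor do they support a claim that many participants are affected.

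**Conclusion.** The mismatch between entry and dosing is real and modest in size. The stated entry rule can admit someone who already meets the protocol's own stop rule, but only if CrCl is Cockcroft-Gault or similar, and then only at about 70 years or older and below roughly 50–58 kg with creatinine just under the cut-off. Overlap with the reduced-dose band is much broader, covers ordinary ages and weights near the cut-off, and holds under all three formulas tested.

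The main consequence is a randomised arm 1 participant who is untreated or on a reduced dose, some dilution of the primary contrast, and a dose subgroup mixed with baseline renal function. The number affected is probably small. The result rests on the assumed formulas and weights. The sample size calculation is not touched.

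**What to change.** Reconcile Selection of participants, Metformin dosing and Safety assessments on one named renal measure and formula, so that the entry criterion and the protocol's own stop criterion agree. Have the sponsor state whether people already in the reduced-dose band at screening are eligible. Which measure and which limits apply is for the sponsor to decide.

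The data are already there: creatinine and eGFR come with the screening chemistry, weight is recorded at screening (Table 1, footnote i), and age is known from the eligibility check. The cost is a change of wording and possibly a few more screen failures.
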